**Methods:**

In a convergent, parallel, mixed-methods, multi-center study design, patients' and health care providers' perspectives assessed by qualitative methods will be triangulated with the results of a quantitative prospective cohort study at six EDs in Berlin, Germany. This study includes four working modules: (1) a systematic literature review; (2) qualitative semi-structured interviews with patients (*n*∼15–20), as well as four focus group interviews with health care providers (*n*∼5); (3) a prospective multi-centre cohort study in adult, self-referred emergency patients at two time points (t0: *n* = 1,031; t1: *n* = 344), primary endpoint: proportion of patients treated other than standard emergency care, secondary endpoints: secondary efficiency, patient-reported outcome measures (PROMs), patient safety, quality of care, clinical outcomes, and cost-effectiveness; participant observation of patients' treatment trajectories and organizational processes at three different patient navigation models (*n*∼10–15), an online provider survey; and (4) data triangulation and recommendations for practice and policy.

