##### Outcomes and measures

2.3.4.2

In module 3, primary and secondary outcomes will be collected, see Table 2.

**Table 2 T2:** Overview of outcomes of module 3 of the NODE study.

Outcome	Concept	Instrument/parameter	Time point of measuring & sample size
Primary outcome			
	Effectiveness of the care model	Proportion of patients that are actually treated (study arm 1 and 2)—or could have been treated (study arm 3) in an alternative outpatient emergency care model instead of in the ED	t0 (*n* = 1,031)
Secondary outcomes			
	Efficiency of care model	Proportion of cases who are actually treated in the alternative care structure without being referred back to the ED.	t0 (*n* = 1,031)
	Process quality	Process times (e.g., duration of treatment, time until diagnostic measures are available/discharge), frequency of diagnostic procedures	t0 (*n* = 1,031) & t1 (*n* = 344)
	Patient safety	Adverse events: Mortality, unplanned (re-)admission to the ICU, unplanned inpatient admission, unplanned re-attendance at the ED within 30 days	t0 (*n* = 1,031) & t1 (*n* = 344)
	Patient satisfaction	ZUF-8 (29)	t1 (*n* = 344)
	Health-related quality of life	EQ-5D-5l (34)	t1 (*n* = 344)
	Costs and Cost-effectiveness	Costs calculated based on utilization of: hospital stays, outpatient visits, inpatient stays, medication/pharmaceuticals, adjuvants and devices, diagnostic and therapeutic measures, total costs in relation to primary outcomes	t1 (*n* = 344)
	Further clinical outcomes (analysis depending on the sufficient number of cases)	Length of inpatient stay, frequency of ICU stay, length of ICU stay at t0 and t1, if applicable.	t0 (*n* = 1,031) & t1 (*n* = 344)

ED, emergency department; EQ-5D-5l, 5-level EQ-5D version of the EuroQoL group questionnaire; ICU, intensive care unit; ZUF-8, “Fragebogen zur Messung der Patientenzufriedenheit” = Zurich patient satisfaction questionnaire. T0 = baseline, t1 = follow up. Study arm 1 = hospital-owned separate outpatient care model within the ED premises or on the hospital grounds; study arm 2 = urgent care practice of the Regional Association of SHI Physicians at the ED location; study arm 3 = ED with standard care model and prospective assessment of patient-care and urgency levels by ED doctors.

##### Power calculation in module 3

2.3.4.3

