The power calculation is based on the primary endpoint—effectiveness of the care model, which is operationalized as the proportion of patients that are treated or could have been treated (study arm 3) in an alternative care structure other than regular ED care: A total sample size of 1,031 patients was confirmed to be recruited among the six study centers. The primary endpoint will be collected based on documented patient flows by study personnel and from secondary data of the respective study centers. The final approach needs to be adapted to local data availability at the study sites. The assumptions on the frequencies of the primary endpoint do not refer to all ED patients, but to the population matching the inclusion and exclusion criteria of the study which is estimated at 50% of all ED patients, based on scientific literature (35, 36). We assume that different proportions of patients with clinically low-acuity consultation needs will be treated in the three different patient navigation models. Assumptions for power calculation purposes were derived from scientific literature (1–7, 9, 37–41) and expert opinion: Study arm 1) The hospital-owned separate outpatient care facility within the ED premises or on the hospital grounds is suspected to lead to a reduction of 30% of ED visits; Study arm 2) Approximately 50% of all ED cases are assumed to be treated by the urgent care practice of the Regional Association of SHI Physicians at the ED location; Study arm 3) The proportion of patients in standard care who could potentially be treated in an alternative care structure is estimated at 70%. Therefore, to detect differences between study arms with a power of 80% and an alpha error of 5%, a sample size of *n* = 31 patients per study arm is required. Despite the low number of participants to determine the difference between study arms, we still aim for a higher precision to estimate the frequencies of the primary endpoint in the study arms. A precision of 5% based on the binomial 95% confidence interval is assumed. This results in different sample sizes per arm:

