Descriptive analyses will be performed among the total patient cohort and within the study arms for patient characteristics, as well as for primary and secondary endpoints. Relative and absolute frequencies will be reported for categorical variables, whereas for quantitative variables mean and standard deviation will be reported in case of normal distribution, median and inter quartile ranges for not normally distributed variables. The chi-square test will be used to investigate differences between study arms for categorical variables, while an analysis of variance (ANOVA; in case of normal distribution) or Kruskal–Wallis-Test (in case of no normal distribution) will be used to detect differences between study arms for quantitative variables. The evaluation of the primary endpoint—effectiveness (i.e., proportion of patients who actually were or potentially could be treated in the alternative outpatient emergency care model) will be carried out using a chi-square test and binomial 95% confidence intervals. Furthermore, factors associated with primary and secondary endpoints will be investigated. For continuous endpoints, analysis of covariance (ANCOVA) will be applied while binary endpoints will be analyzed by logistic regression or Poisson regression analyses. Survival analyses will be performed using Cox regression and Kaplan–Meier analysis. In case of significant associations between socio-demographic variables and secondary outcomes, a stratified analysis will be conducted. Non-parametric methods are used depending on the distribution of variables. Generalized linear mixed models (GLMM) and generalized estimating equations (GEE) are used for longitudinal data. In these analyses, *p*-values are interpreted exploratively, not corrected for multiple testing, and appropriate effect size measures are used.

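### The primary endpoint is realised treatment in arms 1 and 2 but judged suitability in arm 3, so the planned three-arm chi-square test cannot compare effectiveness

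*Protocol article*

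**What the plan says.** Table 2 in section 2.3.4.2 defines the single primary outcome as the proportion "actually treated (study arm 1 and 2)—or could have been treated (study arm 3) in an alternative outpatient emergency care model". Section 2.3.4.3 names it in the same way for sizing: "The power calculation is based on the primary endpoint—effectiveness of the care model".

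The sources differ by arm. Section 2.3.4.3 says "The primary endpoint will be collected based on documented patient flows by study personnel and from secondary data of the respective study centers". For arm 3, section 2.3.4.7 states that the endpoint rests on doctors' assessments of urgency and potential level of care. Section 2.3.4.1 and Table 1 place that assessment in arm 3 only.

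The planning values in section 2.3.4.3 are 30% for arm 1 and 50% for arm 2, both for patients treated in the alternative structure. For arm 3 the text reads "The proportion of patients in standard care who could potentially be treated in an alternative care structure is estimated at 70" percent. From these the protocol derives 31 patients per arm to detect differences between arms. It then sets larger numbers (323, 385 and 323, total 1,031) for a precision of 5 points within each arm.

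Section 2.3.4.6 describes one proportion covering patients who were, or potentially could be, treated in the alternative model, and says its evaluation "will be carried out using a chi-square test and binomial 95% confidence intervals". The abstract's discussion says the study will compare navigation models with standard ED care and evaluate their effectiveness.

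**The concern.** A chi-square test across arms asks whether one proportion is the same in each arm. Here the proportion is not one quantity. In arms 1 and 2 it depends on how many patients were suitable and on how many of those the model diverted. In arm 3 it depends on suitability alone, because no patient is diverted under the arm's definition.

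A model that diverts fewer patients than are suitable will therefore differ from arm 3 even if the patients are the same everywhere. A significant result would not show that the two navigation models differ from each other, or that either does better than standard care. The statement at stake is the study's headline one, a comparison of navigation models with standard ED care on effectiveness.

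**Working it through.** **Inputs.** Planning proportions 30%, 50% and 70%, alpha 5%, power 80%, 31 per arm and precision 5 points (section 2.3.4.3). Planned sizes 323, 385 and 323 (end of the same section). Chi-square test (section 2.3.4.6).

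**1. The precision sizes.** n = 1.96² × p(1 − p) / 0.05².
- p = 0.30 or 0.70: 322.7, rounded up to 323.
- p = 0.50: 384.1, rounded up to 385.
- Sum: 323 + 385 + 323 = 1,031. The protocol's figures reproduce.

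**2. The 31 per arm.** For a 3 × 2 Pearson chi-square test (2 degrees of freedom), the noncentrality is λ = Σ nᵢ(pᵢ − p̄)² / [p̄(1 − p̄)]. With equal arms p̄ = 0.50, so λ = n × (0.04 + 0 + 0.04) / 0.25 = 0.32n.
- n = 30: λ = 9.60, power 79.8%.
- n = 31: λ = 9.92, power 81.2%.

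So 31 is the smallest size that reaches 80%. The pairwise calculations give other numbers:

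| Contrast | n per arm for 80% power |
|---|---|
| 30% vs 50% (arms 1 and 2) | 93 (103 with continuity correction) |
| 50% vs 70% (arms 2 and 3) | 93 |
| 30% vs 70% (arms 1 and 3) | 24 (29 with continuity correction) |

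Of the calculations tried, only the three-arm test returns 31. The sizing therefore counts arm 3 as a comparator.

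**3. What the test does when the two navigation models are identical.** Assume arms 1 and 2 both divert 50%, and arm 3 has its planned 70% potential, at 323, 385 and 323.
- p̄ = (161.5 + 192.5 + 226.1) / 1,031 = 0.563.
- λ = 36.1, power above 99.9%.

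With arms 1 and 2 both at an assumed 40%:

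| Arm 3 potential (assumed) | Power of the three-arm test |
|---|---|
| 50% | 77% |
| 55% | 98.6% |
| 60% to 70% | above 99.9% |

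A gap of 10 to 15 points between suitability and uptake is enough to make rejection likely or near certain, with no difference between the models.

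**4. Why the gap does not measure performance.** Suppose suitability were 70% in every arm (an assumption). Then 30% and 50% realised treatment would mean that 0.30/0.70 = 43% and 0.50/0.70 = 71% of suitable patients were diverted. Because suitability is assessed in arm 3 only, the planned data cannot separate this from a difference in patient mix.

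**5. The contrast that uses one variable.** Arm 1 versus arm 2 at 30% versus 50% with 323 and 385 patients: λ = 29.1, power above 99.9%, treating patients as independent.

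**The case against.** The strongest reply is that nothing is hidden. The split definition is stated in Table 2 and in the power and analysis sections. The arm 3 assessment uses a validated form. The discussion explains that arm 3 replaced a partner practice model that could not be implemented. One research question is a descriptive question about urgency and level of care in standard care EDs. The total of 1,031 comes from precision within each arm, and p-values in the module 3 analyses are to be read exploratively.

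Much of this stands. The arithmetic is right, and each arm's proportion with its confidence interval is a valid estimate. But disclosure, a validated form and exploratory reading do not turn suitability and uptake into the same variable, and no section keeps arm 3 out of the test.

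Four stronger readings are tempting and should not be made.
- *Standard care will be ranked most effective.* The order 70%, 50%, 30% is a planning expectation, and no section says that a higher arm 3 value means a better model.
- *The sign reverses.* The abstract gives "primary endpoint: proportion of patients treated other than standard emergency care", from which a reader might set arm 3 to 0%. That is a shortened phrase. The body consistently includes the potential component for arm 3 and never gives 0%.
- *The efficiency endpoint has the wrong n.* It is defined as "Proportion of cases who are actually treated in the alternative care structure without being referred back to the ED" and stands beside 1,031. That column gives the size of the cohort at t0, not each endpoint's denominator. The same number stands beside length of ICU stay.
- *Differences in ascertainment are confounded with arm through the sites.* The protocol says "The final approach needs to be adapted to local data availability at the study sites", but no section allocates the six centres to arms, so this cannot be shown.

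**Conclusion.** The concern holds for the between-arm test. The plan tests realised treatment against judged potential as one proportion, and its 31 per arm belongs to that test. At the planned sizes the test would reject with more than 99.9% power even if arms 1 and 2 were identical at 50% and arm 3 stood at 70%. It therefore cannot support the stated comparison of navigation models with standard ED care on effectiveness.

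The 70% is the protocol's planning value. The common 50% or 40% in arms 1 and 2 and the range for arm 3 potential are assumptions made for illustration. All power figures treat patients as independent, so correlation within centres would lower them. The sample size of 1,031 is not in question.

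**What to change.** - **Section 2.3.4.6:** limit the between-arm primary test to arm 1 versus arm 2 on realised treatment in the alternative structure. Report arm 3 as a separate one-sample estimate with its 95% confidence interval (about ±5.0 points at n = 323).
- **Section 2.3.4.3:** state that 31 per arm does not apply to this contrast. At 30% versus 50% it needs about 93 per arm for 80% power, which 323 and 385 exceed by a wide margin.
- **Table 2, abstract and discussion:** call the arm 3 quantity diversion potential rather than effectiveness, and word the claim of comparison with standard care to match.

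The cost is wording only, with no new patients or procedures. There are two drawbacks. There would be no p-value against standard care on this endpoint. The change would also come late: recruitment for the cohort was planned to end on 8/31/2024 and the protocol was published after data collection began, so the change and its reason should be documented.

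An alternative is to make the same doctor assessment in all arms and compare realised treatment among suitable patients. That would answer more, but it needs data that the plan does not collect in arms 1 and 2.

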#### Module 3: prospective multi-center cohort study, participant observation and provider online survey

2.3.4

##### Prospective multi-center cohort study in module 3

2.3.4.1

Primary data will be collected at two different time points: t0, at the initial visit of the ED or an alternative care structure, and at t1, a 30-days follow-up. Primary data will be collected by means of a patient survey at t0 in the ED and waiting rooms. As this is an observational study, the routine course of treatment is not interrupted at any time and there are no safety concerns to consider regarding study procedure. Safety endpoints are assessed to evaluate the safety of the different study arms.

At t1, primary data collection will be conducted by online survey or telephone interview. Patient questionnaires for t0 and t1 are available in two languages: German and English. While validated translations for items were used whenever possible, the majority of instruments were translated using an adapted approach to the TRAPD method: This approach involved relying on two independently produced translations, which were created with the assistance of the KI-based translation service of DeepL™ (deepl.com), a bilingual review panel with expertise in both the subject area and research methods supported the translation process (28).

At both time points, t0 and t1, patient-reported outcome and experience measures (PROMs, PREMs) are collected, e.g., reasons for ED visit at t0, and satisfaction with care (ZUF-8) (29) and health system responsiveness at t1 (30). Patient-reported outcome and experience measures are complemented by measurements of baseline socio-demographics and—economics as well as navigational health literacy (NAV-HL) (31) at t0. Secondary data will be extracted, if applicable, from clinical records and from the hospital information systems and the outpatient care unit documentation system at t0. Information on resource use and costs at t0 as well as self-reported health service utilization at the 30-days follow-up (t1) are used for a health economic evaluation. In study arm 3, the assessment of patient urgency and level of care will be measured and documented using a validated assessment form for expert evaluation (32).

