A supplementary part of module 3 is the development and validation of a standard item to measure reasons for low-acuity ED attendances based on international findings and on theoretical reference to the Behavioral Model of Health Care Utilization (33). See Table 1 for a schedule of enrolment, interventions and assessments in module 3.

**Table 1 T1:** Schedule of enrollment, interventions, and assessments of module 3 of the NODE study.

	Study period			
	Enrollment	Data collection period		Close-out
TIMEPOINT	0	*t_0_ (Baseline)*	*t_1_ (30 days follow-up)*	*month 20 until 36*
ENROLLMENT module 3:				
Eligibility screening	X			
Written informed consent	X			
Survey participation		X	X	
Dissemination				X
ASSESSMENTS:				
Baseline variables	X	X		
Questionnaire		X	X	
Participant observation		X		
Urgency and care level assessement (study arm 3)		X		
Secondary data extraction		X	X	
DATA ANALYSES				X

t0 = baseline, t1 = follow up.

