Study arm 1: Assumed frequency of the primary endpoint 30%—*n* = 323Study arm 2: Assumed frequency of the primary endpoint 50%—*n* = 385Study arm 3: Expected incidence of primary endpoint 70%—*n* = 323This gives a final sample size of *n* = 1,031. The aim is that approximately one third of the recruited patients (*n* = 344) will consent to and successfully complete a follow-up survey 30 days after their emergency department visit (t1). Equal numbers for t1 across all study arms enable comparisons for exploratory analyses of secondary endpoints. This estimate is based on the assumption that approximately 50% (*n* = 516) of the patients will agree to a follow-up interview, of which a further 17% (approximately *n* = 172 patients) will be unavailable or unable to complete the interview successfully for other reasons.

##### Participant observation of patient treatment paths and organizational processes in module 3

2.3.4.4

Participant observations (*n*∼10–15) will explore and document treatment paths of patients in the different navigation models of three study arms. These observations will result in digital protocols and digital patient flow diagrams. The aim of the participant observations is the in-depth exploration of model differences, patients' expressed treatment experience, their treatment paths, behavior and navigation within the respective care settings as well as provider-patient interaction. Participant observations will capture the structural and processual differences within and between study arms and hereby provide context-sensitive data for triangulation with the qualitative interviews and the multi-center cohort study, particularly with regard to model performance in terms of efficiency and patient safety, patient satisfaction (29) and measures of navigational health literacy (31) as well as health system responsiveness (30).

##### Provider online survey in module 3

2.3.4.5

An exploratory and anonymous quantitative online survey among a subgroup of health care providers working in the context of emergency care in Germany will be conducted, distributed by the professional networks of the authors. The survey aims to investigate which patient navigation models in emergency care and instruments are used at different locations in Germany and how providers assess the efficiency of these models.

##### Data analysis plan of module 3

2.3.4.6

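### The t1 part of the 30-day safety outcomes is assigned to the 344 survey completers, and the article contradicts itself on whether site records are extracted after t0

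*Protocol article*

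**What the plan says.** Four places in the protocol article bear on this.

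- **Section 2.3.4.2, Table 2.** The patient-safety row reads "Adverse events: Mortality, unplanned (re-)admission to the ICU, unplanned inpatient admission, unplanned re-attendance at the ED within 30 days". Its time point and sample-size entry is "t0 (*n* = 1,031) & t1 (*n* = 344").
- **Section 2.3.4.3, power calculation.** The 344 are defined by survey completion: "approximately one third of the recruited patients (*n* = 344) will consent to and successfully complete a follow-up survey 30 days after their emergency department visit". The route to that number is that "approximately 50% (*n* = 516) of the patients will agree to a follow-up interview", and that "a further 17% (approximately *n* = 172 patients) will be unavailable or unable to complete the interview successfully for other reasons".
- **Section 2.3.4.1, cohort description.** "At t1, primary data collection will be conducted by online survey or telephone interview". Routine data are to be taken, where applicable, from clinical records and "from the hospital information systems and the outpatient care unit documentation system at t0". Health-service use over the 30 days is described as self-reported.
- **Section 2.3.4.1, Table 1.** The row "Secondary data extraction" carries a mark at t0 and another at t1.

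The data management section (2.3.4.7) has study nurses extracting hospital-record items, including inpatient stay and discharge, that can be linked to the survey. Its examples include no vital-status item.

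**The concern.** An outcome should not decide whether it is observed. A patient who dies between the index visit and day 30 cannot complete the survey that defines the t1 sample. A patient in hospital or intensive care at day 30 may be less able to. If t1 safety is read from survey completers, post-index mortality is zero in every arm whatever the truth, and the other components depend on who chose to reply.

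This matters because the introduction names missing patient-safety evidence as a major concern about these models. Section 2.3.4.1 says the safety endpoints are there to evaluate the arms, and section 2.3.4.6 sets patient safety against costs in the cost-effectiveness analysis. Reporting no deaths at t1 would look reassuring but carry no information.

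The remedy may already be scheduled, since Table 1 has a t1 extraction. The article does not say whom that extraction covers or which outcomes it feeds, and the text of 2.3.4.1 does not mention it.

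**Working it through.** **1. Reproduce the plan's figures.**

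- Total: 323 + 385 + 323 = 1,031.
- t1 sample: 1,031 / 3 = 343.7, rounded to 344; also 516 − 172 = 344.
- The 17% step works only as a share of everyone recruited (172 / 1,031 = 16.7%). As a share of those who agree it is 172 / 516 = 33.3%. This is a matter of wording and does not change the 344.
- Patients without a t1 survey: 1,031 − 344 = 687, or 67%.
- Equal t1 numbers per arm, as the article intends: 344 / 3 ≈ 115.

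**2. Set the passages side by side.** t0 is the initial visit, so events after the index episode belong to t1.

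| If this governs | Source of post-index events | Consequence |
|---|---|---|
| Text of 2.3.4.1 with Table 2 | Survey only, n = 344 | Post-index deaths cannot be seen; other events come from completers only |
| Table 1 | Survey plus site records | The 344 in Table 2 is wrong or unexplained for events that records can show |

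Either way, one passage has to change.

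**3. Mortality.** The article describes no proxy respondents. A death before day 30 therefore removes the patient from the completers, and the count among completers is 0 by construction. A telephone call might reveal a death, but that patient would still not be one of the 344.

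**4. Precision.** The article gives no event rates, so 5%, 10% and 15% are assumptions. The 95% half-width is 1.96 × √(p(1 − p)/n).

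| Assumed rate | n = 115 per arm | n = 323 (arms 1, 3) | n = 385 (arm 2) |
|---|---|---|---|
| 5% | ±4.0 points | ±2.4 | ±2.2 |
| 10% | ±5.5 | ±3.3 | ±3.0 |
| 15% | ±6.5 | ±3.9 | ±3.6 |

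Example: 1.96 × √(0.09/115) = 5.5 points; 1.96 × √(0.09/323) = 3.3 points.

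If no event is seen, the one-sided 95% upper bound is 1 − 0.05^(1/n): 2.6% at n = 115 and 0.9% at n = 323. The two-sided exact limits are 3.2% and 1.1%.

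The rate distinguishable from 10% between two arms (two-sided 5%, 80% power) solves n = [1.96√(2p̄(1 − p̄)) + 0.842√(p₁(1 − p₁) + p₂(1 − p₂))]² / (p₂ − p₁)². This gives about 23.8% with 115 per arm and 17.6% with 323.

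**5. Selection.** Let patients with an event reply at r times the rate of those without. The rate seen among completers is p·r / (p·r + 1 − p). For a true 10%:

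- r = 0.5: 0.05 / 0.95 = 5.3%
- r = 1: 10%
- r = 1.5: 0.15 / 1.05 = 14.3%

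The article gives no basis for choosing r, so this shows sensitivity and is not an estimate of bias.

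**The case against.** The strongest reply is that Table 1 does schedule a t1 extraction, and that 2.3.4.1 says records are taken at t0 without saying only at t0. Section 2.1 is also compatible with later extraction: module 3 data collection runs 22 months and includes routine-data extraction, while cohort recruitment runs 15 months (6/1/2023 to 8/31/2024). Compatibility is not confirmation, and the 344 in Table 2 would still need explaining.

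It can also be said that the t1 comparisons are declared exploratory, that the primary endpoint is measured at t0 in everyone, and that a condensed article may leave data sources to the full protocol. The first two points limit the consequences. But an exploratory label does not make a death observable by survey, and the issue here is a conflict between statements in the article rather than an omission.

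A reader might infer three stronger conclusions that the document does not support:

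- **That deaths cannot be observed at all.** The safety row also lists t0 with 1,031, so deaths and admissions in the index episode can come from records with the full denominator.
- **That readmission and re-attendance will be biased towards safety.** Patients who return might reply less or more often. If selection were the same in each arm, its effect on between-arm contrasts would differ from its effect on absolute rates.
- **That complete 30-day records exist for all 1,031.** Extraction is qualified as where applicable, and the article does not say that baseline consent covers records to day 30. Site records would also miss deaths at home and attendances elsewhere.

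**Conclusion.** The point holds as an internal contradiction with a real consequence on one of its two readings. On the reading given by 2.3.4.1 and Table 2, post-index mortality is unobservable among completers; this follows from logic, provided no proxies respond. The other post-index components rest on 344 of 1,031 patients, with selection of unknown size and direction and per-arm intervals about 1.7 times as wide as with 323 patients (√(323/115) = 1.68). The interval widths rest on assumed event rates of 5% to 15% and on 115 completers per arm. Index-episode safety events and the primary endpoint are not affected. On the Table 1 reading most of the problem can be repaired, but the stated denominator is then wrong for record-based events and the source of vital status is still unstated.

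**What to change.** 1. Reconcile the text of 2.3.4.1 with Table 1 so that site records are extracted up to day 30 for all enrolled patients, where consent and local data allow.
2. In Table 2, set the denominator for record-based safety events to 1,031 and state the source of each component.
3. Base the between-arm safety comparison on record-based events ascertained the same way in everyone. Report self-reported events at other hospitals among the 344 separately, as a supplementary analysis. Adding them to the main count would give completers fuller ascertainment than non-completers.
4. Do not report survey-based 30-day mortality. Name a vital-status source other than the survey, or restrict the outcome to deaths recorded at the sites and label it so.

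The cost is some extra extraction time by study nurses who already work with these records, plus a check that consent covers the later period. Unless a further source is added, deaths at home and events at non-participating hospitals will remain incompletely captured, and the report should say so.
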